##### LSVT LOUD®

The LSVT LOUD® intervention is prescriptive and consists of four 50-min sessions per week delivered over 4 weeks [36]. Each session follows a similar structure: 25 min of repeated and intensive maximum-effort drills, and 25 min of high-effort speech production tasks [36]. Participants will also be set 5 to 10 min of home-based practice tasks on treatment days, and up to 30 min of home-based practice tasks on non-treatment days [37].

Content will consist of repeated repetitions of sustained ‘ah’ phonation, maximum fundamental frequency-range high- and low-pitch glides, and functional sentence repetition for the first half of each session, and exercises using speech production hierarchy that progresses throughout duration of the treatment programme (single word, phrases, sentences, paragraph reading, conversation) during the second half of the sessions [37]. Throughout all of the sessions, the focus of the intervention will be to ‘think loud’, maintaining the vocal loudness produced during vowel phonation throughout all other tasks during the treatment [36].

Sessions will be conducted by a suitably trained speech and language therapist or therapy assistant on a one-to-one basis. Sessions may take place in out-patient clinics, the participant’s home or remotely using tele-LSVT software. Once the exercises have been established, LSVT LOUD® may be delivered using the LSVT companion software for a proportion of the time, in line with local practice.

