#### Adverse events

A risk assessment of the PD COMM trial has been performed with the SLT interventions considered to be of low risk. From the literature, the only reported AE associated with the interventions was a small increased risk of vocal strain or abuse; however, none were reported in the PD COMM Pilot trial. This risk will be minimised: speech and language therapists are trained to identify and rehabilitate vocal strain so, if present, the therapist will be able to identify and address it. No other risks are expected to arise from taking part in the trial. It is, therefore, reasonable to collect only targeted AEs.

For participants in either therapy arm, any vocal strain or abuse believed to be associated with treatment will be identified by the therapists at the participants’ therapy session and will be reported in the AE log.

In all trial arms, BCTU will also check the participant-reported resource usage form to ensure that no vocal strain or abuse has occurred following participants reporting out-patients appointments with ear, nose and throat (ENT) specialists. At the 12-month clinical visit, the medical professional will also check whether any AEs have occurred since entering the trial.

Serious adverse events (SAEs) are events that cause death, are life-threatening, require or extend an existing hospitalisation, result in persistent or significant disability or incapacity; or, are otherwise considered medically significant by the investigator. SAEs that are not related to vocal strain or abuse are excluded from expedited notification during the course of the trial and will be collected in the resource usage and 12-month clinical case report form (CRF).

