#### Data collection

Data is collected in clinic at baseline and 12 months post randomisation at usual clinic appointments, and patient-reported outcome data is also collected at 3, 6 and 12 months post randomisation by postal questionnaires to the participant which are returned directly to BCTU. Participants who do not comply with their treatment allocation will be followed up as other participants unless they chose to withdraw from the trial. Data is reviewed on receipt, and return rates and completeness are closely monitored throughout the trial to ensure patient retention. The Trial Management Group review return and completeness rates and can determine whether to trigger further review or monitoring.

Figure 1 provides a flowchart of the trial design and Table 2 denotes the schedule of events. Data is sent to BCTU where they are securely held in restricted-access areas and entered onto a bespoke trial database. For participants randomised to the intervention arms, further data around the interventions including therapy logs and therapy notes is sent to BCTU (see below). Redacted therapy notes and anonymised data sets will be sent to researchers at Glasgow Caledonian University for the intervention description analysis. This data will be integrated with the process evaluation data collected and held at the University of Bangor.

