#### Health economics analysis

The economic evaluation will estimate the cost-effectiveness of LSVT LOUD® or standard NHS SLT compared to no SLT treatment (control) in PD. The base-case economic evaluation will be undertaken from the UK NHS and personal social services (PSS) perspective, with further analysis from a broader societal perspective, over 12 months’ follow-up.

A cost-effectiveness analysis will use the primary outcome (VHI) to calculate the cost per unit improvement in VHI score, and a cost-utility analysis will use responses from the EQ-5D-5 L to calculate cost per quality-adjusted life year (QALY) gained. Resource-use data will be collected on PD-related medication, primary care and secondary care healthcare utilisation, including the use of therapy services, and use of social services including formal care. Further information will be collected on time off work, participant out-of-pocket costs and costs incurred by informal carers, in order to inform analysis from a societal perspective. The cost of delivering the LSVT LOUD® intervention and NHS SLT, including length and number of sessions and any training required will be determined within the trial. Data will be collected using a participant-completed resource utilisation questionnaire (at 3, 6 and 12 months) and the therapist-completed initial interview logs and treatment record forms. Unit costs from routine sources will be applied to resource-use data [46, 47]. Health-related quality of life will be assessed using the EQ-5D-5 L [41] collected at baseline, 3, 6 and 12 months. The crosswalk value set will be applied to patient responses to obtain utility scores, in line with current NICE recommendations and QALYs calculated using the ‘area under the curve’ approach. The ICECAP-O [42] will also be used to capture changes in participants’ capabilities, allowing a broader assessment of benefits to patients.

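### Expedited SAE notification depends on event type (vocal strain or abuse), not on relation to the therapy, so a serious unforeseen event attributed to either SLT intervention is excluded from it

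*Protocol article*

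**What the plan says.** All of the following is from the protocol article.

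- **Definition.** The Adverse events section defines SAEs by seriousness alone: "Serious adverse events (SAEs) are events that cause death, are life-threatening, require or extend an existing hospitalisation", with further criteria of the same kind. Causality is not part of the definition.
- **Notification rule.** The same section then states: "SAEs that are not related to vocal strain or abuse are excluded from expedited notification during the course of the trial". The excluded events go to the resource usage form and the 12-month clinical case report form.
- **Rationale.** The interventions were assessed as low risk. In the literature "the only reported AE associated with the interventions was a small increased risk of vocal strain or abuse", none was seen in the pilot, and no other risk is expected. Only targeted AEs are therefore collected.
- **Where causality appears.** The section refers to a link with treatment only for vocal strain or abuse that therapists enter in the AE log.
- **Timing of the other routes.** Under Data collection, "patient-reported outcome data is also collected at 3, 6 and 12 months post randomisation by postal questionnaires to the participant". Table 2 and the Health economics analysis section place the participant-completed resource usage questionnaire at the same three times. A medical professional checks for AEs in general once, at the 12-month visit.

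**The concern.** Expedited notification is useful mainly for a serious event that someone believes the intervention caused, above all one that nobody predicted. The stated rule selects on a different variable. A serious event linked to the one known harm is notified promptly. A serious event of any other kind waits, even when the person who saw it attributes it to the session.

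Take a participant admitted to hospital with a non-voice event that begins during the LSVT LOUD session component described as "25 min of repeated and intensive maximum-effort drills". The therapist thinks the session caused it. A site that follows the sentence as written makes no expedited report.

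The expectation that no other risks will arise cannot carry this exclusion, because an unexpected related event is what would contradict that expectation. At stake is how quickly a new harm would be recognised while people are still being randomised to the therapy.

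**Working it through.** The plan gives no figure on this point. The check compares the rule with each described reporting route, then sizes the delay.

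**1. Does any described route give a related non-voice SAE prompt notification?**

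- AE log (Adverse events; Table 2, note c): therapy arms only, and described only for vocal strain or abuse.
- Trials unit check of resource usage forms (Adverse events): described as looking for vocal strain or abuse after ENT appointments.
- Resource usage form: completed by the participant at 3, 6 and 12 months, with no causality judgement described. A participant who has died or is incapacitated may not return it.
- Session records and therapy notes (Treatment dose and fidelity; Data collection): the notes are sent when trial treatment is complete, and their stated use is describing the intervention.
- 12-month visit: one general AE check.

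None of these is a prompt route for such an event.

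**2. How long is the wait?**

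- The forms fall at months 3, 6 and 12. The wait to the next form is therefore up to about 3 months for events before month 6, and up to about 6 months for events between months 6 and 12.
- LSVT LOUD should start within 7 weeks of randomisation and lasts 4 weeks. A course started at week 7 ends at 7 + 4 = week 11. The 3-month form falls at about week 13, so the wait is between 13 − 11 = 2 and 13 − 7 = 6 weeks.
- A course started earlier has a longer wait, at most the full 3 months.
- Standard NHS SLT should start within 4 weeks and is unlikely to exceed 12 weeks, so it can run to about 4 + 12 = week 16. An event just after the 3-month form waits for the 6-month form, again up to about 3 months.

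**3. How many people are randomised meanwhile?**

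- Planned rate (Sample size; Trial status): 546 people from 11 October 2016 to 30 November 2020, about 49.6 months. 546 / 49.6 = 11.0 per month.
- Achieved rate (Discussion; Trial status): 329 people by 10 September 2019, about 35.0 months. 329 / 35.0 = 9.4 per month.
- With 52.2 / 12 = 4.35 weeks per month, these are 11.0 / 4.35 = 2.53 and 9.4 / 4.35 = 2.16 per week.

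| Case | Wait | Randomised meanwhile |
|---|---|---|
| LSVT LOUD course started at week 7, shortest wait, achieved rate | 2 weeks | 2 × 2.16 = 4 |
| Same course, longest wait, planned rate | 6 weeks | 6 × 2.53 = 15 |
| Event close to randomisation, achieved rate | 3 months | 3 × 9.4 = 28 |
| Event close to randomisation, planned rate | 3 months | 3 × 11.0 = 33 |

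Allocation is 1:1:1, so one third of each count goes to any one arm and two thirds to therapy. In the upper-bound case that is about 19 to 22 people allocated to therapy.

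**The case against.** The strongest reply has three parts.

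**The full protocol is not shown.** The article condenses version 4.0, where causality assessment and reporting lines would normally be set out. This stands as a limit: version 4.0 may contain a route for related or unexpected SAEs. It does not dispose of the point, because the article has not merely left a detail out. It states an exclusion without exception. If the full protocol differs, the article's sentence is wrong and needs correcting.

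**The rule is a reasoned, risk-based choice.** It rests on a formal risk assessment, a single harm known from the literature, and no vocal strain in a pilot that randomised 89 people. That supports light collection of non-serious events and suggests related SAEs will be rare. It does not support ignoring causality when a serious event has occurred.

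**Information does arrive during the trial.** This stands, and it limits the point. A reader might infer that the trial has no timely signal of a new harm, that the low-risk assessment could not be tested while the trial runs, or that detection normally waits for the 12-month visit. The document supports none of these. Forms come back at 3, 6 and 12 months and go straight to the trials unit, data are reviewed on receipt, and the resource-use data cover secondary care. An LSVT LOUD course on schedule ends before the 3-month form. A delay of a full year would need an event close to randomisation that is then missed on both the 3-month and the 6-month form.

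**Conclusion.** The point holds in a limited form. As written, a serious event attributed to LSVT LOUD or standard NHS SLT is excluded from expedited notification unless it is related to vocal strain or abuse, and no other prompt route is described. The event is delayed, not lost.

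The delay is usually weeks to about 3 months: roughly 4 to 15 further people randomised for an event in an LSVT LOUD course started at week 7, and at most about 28 to 33 for an event close to randomisation. The 12-month case report form is the first capture only when the postal forms are not returned or miss the event.

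These counts assume even recruitment at 9.4 to 11.0 per month, therapy delivered on schedule, and forms that are completed when due and mention the event. Postal return time is not stated and would add to the wait. The practical impact is modest because related SAEs are expected to be few, but the criterion is the wrong one and is easily corrected. The conclusion rests on the article's own text, not on any outside reporting requirement.

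**What to change.** Reword the exclusion in the Adverse events section so that only SAEs judged not related to the trial intervention are excluded from expedited notification. State that the investigator makes that judgement, informed by the therapist where the participant has one. SAEs judged unrelated, whatever their type, stay on the resource usage form and the 12-month case report form as planned. If protocol version 4.0 already contains such a route, amend the article's sentence to agree with it.

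The cost is one reworded sentence, a relatedness assessment, and a reporting route for the few non-voice SAEs suspected to be related. The low-burden design is kept, because hospital admissions and deaths judged unrelated to therapy need no expedited report. The change alters reporting only. It does not touch treatment, eligibility or the analysis.

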#### Data collection

Data is collected in clinic at baseline and 12 months post randomisation at usual clinic appointments, and patient-reported outcome data is also collected at 3, 6 and 12 months post randomisation by postal questionnaires to the participant which are returned directly to BCTU. Participants who do not comply with their treatment allocation will be followed up as other participants unless they chose to withdraw from the trial. Data is reviewed on receipt, and return rates and completeness are closely monitored throughout the trial to ensure patient retention. The Trial Management Group review return and completeness rates and can determine whether to trigger further review or monitoring.

Figure 1 provides a flowchart of the trial design and Table 2 denotes the schedule of events. Data is sent to BCTU where they are securely held in restricted-access areas and entered onto a bespoke trial database. For participants randomised to the intervention arms, further data around the interventions including therapy logs and therapy notes is sent to BCTU (see below). Redacted therapy notes and anonymised data sets will be sent to researchers at Glasgow Caledonian University for the intervention description analysis. This data will be integrated with the process evaluation data collected and held at the University of Bangor.

**Fig. 1 Fig1:**
[figure not shown]
Flow diagram of trial design

**Table 2 Tab2:** Time and event schedule

Measure	Enrolment	Assessment time			
		Allocation t = 0	3 months	6 months	12 months
**Enrolment**					
Informed consent	✓				
Eligibility	✓				
Allocation		✓			
**Interventions**					
Initial interview log and treatment record form (all sessions)			✓^a^		
Home-based therapy diary			✓^b^		
**Assessments**					
Baseline case report form		✓			
VHI; PDQ-39; QASD; EQ-5D-5 L; ICECAP-O		✓	✓	✓	✓
Resource Usage Questionnaire			✓	✓	✓
Global rating score (Transition item)			✓		
PDQ-Carer		✓	✓	✓	✓
Adverse event log			✓^c^		
12-month case report form					✓

^a^Following each therapy session for participants in the two SLT treatment arms only

^b^Completed at home by the participant as recommended in their SLT therapy session

^c^Only required for participants randomised to a treatment arm

Key: *EQ-5D* EuroQol 5-dimension, 5-level questionnaire, *ICECAP-O* ICEpop Capabilities Measure for Older Adults, *QASD* Questionnaire on Acquired Speech Disorders, *PDQ-39* Parkinson’s Disease Questionnaire-39, *SLT* Speech and Language Therapy, *VHI* Voice Handicap Index

#### Treatment dose and fidelity

The speech and language therapists will complete an initial interview log including the Abbreviated Mental Test and intervention record forms at each treatment session for participants receiving SLT. Furthermore, in the LSVT LOUD® arm and where prescribed in the NHS SLT arm, participants will complete home-based therapy diaries. Therapists will also complete standard NHS therapy notes; upon trial treatment completion, a pseudo-anonymised (i.e. participant is only identified by trial number) version of these will be sent to the research team.

#### Process evaluation

In order to evaluate the implementation of PD COMM interventions, a process evaluation will be carried out alongside PD COMM. The process evaluation team led by Bangor University will employ a number of approaches to data collection, including:
Qualitative interviews with PD COMM participantsQualitative interviews with PD COMM therapistsCritical incident reportsTherapist’s questionnaire

A detailed protocol for these analyses including intervention description has been published [45].

The analysis of process evaluation data will focus on the practical implementation of the trial interventions, including how these were tailored to individual patient and other circumstances.

#### Sample size

The primary outcome is the mean difference in the VHI total score at 3 months across the three comparisons: LSVT LOUD® versus control; standard NHS SLT versus control; and LSVT LOUD® versus standard NHS SLT. Data from the PD COMM Pilot trial was used to inform the sample size calculations for this trial as the minimal clinically important difference (MCID) for the VHI has not been established in PD patients. In the PD COMM Pilot trial, a difference of around 10 points in VHI total score was observed at 3 months between SLT and control for both types of SLT (standard NHS and LSVT LOUD®) versus control comparisons. To detect a 10-point difference in VHI total score between arms at 3 months (using a two-sided *t* test and the upper standard deviation of 26.27 obtained from the VHI baseline data from the pilot trial; effect size 0.38), with 80% power and *α* = 0.01, we need 163 participants per arm. Allowing for 10% drop-out will require 182 participants per arm, so 546 participants in total.

#### Statistical analysis

All primary analyses (for both the primary and secondary outcomes) will be by intention to treat. Participants will be analysed in the treatment group to which they were randomised, and all participants will be included whether or not they received the allocated treatment. This is to avoid any potential bias in the analysis. For all tests, summary statistics (e.g. mean differences) will be reported along with 95% confidence intervals and *p* values from two-sided tests. A *p* value of < 0.01 will be considered statistically significant, as per the sample size calculations to take into account the multiple treatment comparisons being undertaken.

There will be no interim analyses.

The analysis and interpretation of qualitative data, and its integration with quantitative data on intervention provision, will be performed between researchers at Bangor University ([name]) and Glasgow Caledonian University ([name]), with input from University College London ([name]) and King’s College London ([name]).

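### Significance is judged at p<0.01 but all tests carry 95% intervals, so any result with 0.01≤p<0.05 shows an interval excluding zero beside a non-significant verdict

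*Protocol article*

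**What the plan says.** Under Statistical analysis, the protocol article fixes one interval level for every test: "summary statistics (e.g. mean differences) will be reported along with 95% confidence intervals", together with p "values from two-sided tests". The next sentence sets the threshold: a p "value of < 0.01 will be considered statistically significant, as per the sample size calculations". The reason given is "to take into account the multiple treatment comparisons being undertaken".

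The Sample size section confirms that 0.01 is the working level. The primary outcome is compared "across the three comparisons: LSVT LOUD® versus control; standard NHS SLT versus control; and LSVT LOUD® versus standard NHS SLT", and 163 participants per arm are derived at α = 0.01 and 80% power. Secondary outcome analyses again names 95% intervals, for the adverse-event relative risks. The article mentions no 99% or multiplicity-adjusted interval, and it does not say how a 95% interval is to be read against the 0.01 threshold.

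**The concern.** A confidence interval and a two-sided test from the same model agree about zero only when the interval level is one minus the test level. Here the test level is 1% and the interval level is 95%. Wherever 0.01≤p<0.05, the report will put an interval that excludes zero next to a statement that the difference is not significant.

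Two things are at stake. First, many readers judge a result by its interval. The Sample size section says that no minimal clinically important difference for the VHI is established in Parkinson's disease, so the estimate and its interval will carry much of the interpretation. The conflict lies below the 10-point target, where a modest real effect would fall. Second, the stricter threshold was chosen because there are three comparisons, and the intervals make no such allowance. As the interval rule covers all tests, the mismatch also reaches the secondary outcomes and the 6- and 12-month results.

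This is not a detail left to an analysis plan. The article states both levels, in adjacent sentences.

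**Working it through.** **Inputs.** Sample size section: difference 10 points, "the upper standard deviation of 26.27 obtained from the VHI baseline data from the pilot trial; effect size 0.38", two-sided α = 0.01, power 80%, 163 per arm, 10% drop-out. Statistical analysis section: interval level 95%, threshold p<0.01. Assumptions: the pilot baseline SD also applies at 3 months, and 163 per arm are analysed. The article gives no baseline-to-3-month correlation, so 0, 0.3, 0.5 and 0.7 are tried.

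**1. The plan's own figure.** Standardised difference = 10/26.27 = 0.381. The exact two-sample t test at two-sided 0.01 needs 163 per arm (power 0.8004). Drop-out: 163/0.9 = 181.1, rounded up to 182, and 3 × 182 = 546. The stated numbers reproduce, so 0.01 is the operative level.

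**2. Half-widths, unadjusted.** SE = 26.27 × √(2/163) = 2.91. With 324 degrees of freedom the critical values are 1.967 (95%) and 2.591 (99%).
- 95%: 1.967 × 2.91 = 5.72 points
- 99%: 2.591 × 2.91 = 7.54 points
- Ratio: 7.54/5.72 = 1.32

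An observed difference between 5.72 and 7.54 gives a 95% interval that excludes zero and a p value of at least 0.01.

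**3. The planned model.** Primary outcome analysis specifies a linear regression adjusted for baseline VHI. For an assumed correlation r, the SD becomes 26.27 × √(1 − r²). The chance of conflict for one comparison is the power at 0.05 minus the power at 0.01, from the noncentral t distribution.

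| r | SD | Conflict band (points) | Chance at true 5 | Chance at true 10 |
|---|---|---|---|---|
| 0 (unadjusted) | 26.27 | 5.7–7.5 | 0.403 − 0.193 = 21% | 0.929 − 0.800 = 13% |
| 0.3 | 25.06 | 5.5–7.2 | 0.435 − 0.217 = 22% | 0.949 − 0.843 = 10.5% |
| 0.5 | 22.75 | 5.0–6.5 | 0.507 − 0.274 = 23% | 0.977 − 0.915 = 6% |
| 0.7 | 18.76 | 4.1–5.4 | 0.670 − 0.428 = 24% | 0.998 − 0.987 = 1% |

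With no true effect the chance is 0.05 − 0.01 = 4%, whatever the SD or correlation.

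**4. Three comparisons together.** The three pairwise differences among three equal arms are correlated. Simulating them with no true differences (2 million draws) gives:
- at least one 95% interval excludes zero: 12.2%
- at least one p<0.01: 2.7%

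These two figures do not depend on the SD or on r.

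**The case against.** The strongest reply is that the plan has exactly one rule for significance, p<0.01, and nowhere uses an interval to declare benefit. A result with p = 0.03 is non-significant under the plan without ambiguity. Showing conventional 95% intervals beside a stricter test level is a defensible way to report estimates. All of this stands.

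Four stronger readings are therefore tempting but unsupported:
- A reader might infer that the plan contradicts its own decision rule or inflates its type I error. It does neither. The 12% figure describes what a reader would meet who used the 95% intervals as tests; it is not the trial's error rate.
- A reader might infer that the intervals understate uncertainty about the size of benefit. A labelled 95% interval keeps its stated coverage for each comparison. What it lacks is joint coverage, which the article does not claim.
- A reader might infer that every non-significant result will clash with its interval. Results with p≥0.05 agree with theirs.
- A reader might take 5.7–7.5 points and 13% at a true 10 points as the figures for the planned analysis. They hold for an unadjusted comparison; the planned baseline adjustment lowers both.

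It can also be said that multiplicity alone does not call for 99%. Bonferroni intervals for three comparisons would be at 98.3% (half-width 7.0 points unadjusted), and at least one would exclude zero in about 4.4% of trials with no true differences. That is right. The argument for 99% is that it mirrors the threshold the trial has chosen.

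What survives is that the article fixes two levels for the same results and says nothing to reconcile them.

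**Conclusion.** The point holds as an inconsistency of reporting and interpretation. It is not a flaw in the test, the power or the sample size. Under the planned adjusted model the conflict band lies somewhere between 4.1–5.4 and 5.5–7.2 VHI points for correlations of 0.7 down to 0.3. A given comparison lands in the band in 4% of trials with no effect and in 21–24% at a true 5 points. At the design difference of 10 points the chance is small if baseline VHI predicts strongly (1%) and at most 13% without any adjustment.

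The band and the chances under a true effect rest on SD 26.27 at 3 months, 163 analysed per arm and the assumed correlations. The 4% figure and the contrast of 12% with 2.7% need only two-sided tests and equal arms. The change is worth making because it costs almost nothing and removes an avoidable ambiguity from the primary result.

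**What to change.** Amend the interval sentence under Statistical analysis so that 99% confidence intervals are reported for the three VHI comparisons and for any other outcome judged at p<0.01. If 95% intervals are also shown, for instance for later meta-analysis, label them as unadjusted for multiple comparisons and state that they are not used to judge significance. Bring the 95% intervals for the adverse-event relative risks, under Secondary outcome analyses, into line or give them the same label.

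The cost is a sentence or two of text. No participants, data or additional models are needed, and 163, 182 and 546 stay as they are. The downside is intervals about 32% wider, for example 7.54 instead of 5.72 points either side of the unadjusted VHI difference.

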### Secondary outcome analyses

The majority of the secondary outcome measures (e.g. PDQ-39) are continuous measurements and will be analysed in a similar way to that described for the primary analysis: a linear regression analysis adjusting for relevant baseline score and all of the minimisation variables (baseline VHI, age and severity of PD). As per the primary outcome, the primary analysis for the secondary outcomes will be based on the 3-month data.

To assess whether any treatment effect is maintained, participant- and carer-completed questionnaires are also being collected at 6 and 12 months post randomisation. Data collected at 6 and 12 months will be analysed using the same methods as described above. Further analysis using a repeated measures model will also be performed using all data over the 3-, 6- and 12-month assessment points.

A global rating scale (Transition item) will be completed by the participant and carer separately at the 3-month time point. This data will be used to calculate an MCID for the VHI in this population.

Adverse events and safety data will be summarised descriptively by treatment arm, and the number of events and percentage of participants experiencing any AE reported. It is not expected that there will be many AEs as a result of the intervention, but the number of participants reporting an AE will be compared using a chi-squared test, with relative risks and 95% confidence intervals reported (if appropriate).

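### The p<0.01 criterion carries no exception for harms, so on the natural reading the adverse-event test is judged at a level sized on VHI and tightened for three comparisons

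*Protocol article*

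**What the plan says.** The Statistical analysis section gives general rules ahead of any outcome-specific text. It begins with primary analyses of both the primary and the secondary outcomes. It then sets a reporting rule: "For all tests, summary statistics (e.g. mean differences) will be reported along with 95% confidence intervals and" p "values from two-sided tests". The next sentence sets the criterion: a p value below 0.01 "will be considered statistically significant, as per the sample size calculations to take into account the multiple treatment comparisons being undertaken". No other significance level appears in the article.

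Three other places bear on harms:

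- Secondary outcomes lists adverse events among the patient-reported secondary outcomes.
- Secondary outcome analyses states that "Adverse events and safety data will be summarised descriptively by treatment arm", with numbers of events and percentages of participants. It expects few events, but adds that "the number of participants reporting an AE will be compared using a chi-squared test", with relative risks and 95% confidence intervals if appropriate.
- Adverse events names one harm known from the literature, "a small increased risk of vocal strain or abuse", and on that ground limits collection to targeted events.

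The Sample size section shows where 0.01 comes from: a calculation on VHI total score alone.

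**The concern.** A stricter significance level lowers the chance of a false positive and raises the chance of a false negative. For a claim of benefit across three pairs of arms, that is the intended trade. For a harm the costlier error is usually the missed signal, and the stricter level makes it more likely. The protocol names a single risk and plans a formal test on it, so that test will produce a verdict. If the verdict is taken at 0.01, an imbalance could be reported as non-significant because of a level chosen for the VHI comparisons.

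The relative risk and its interval are promised only where appropriate. With no events in one arm, a plausible pattern here, the ordinary relative risk is undefined, and the p value may then be the only inferential statement left.

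The point does not depend on how events are ascertained in the control group. It applies equally to LSVT LOUD versus NHS SLT, where therapists keep the adverse-event log in both arms.

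**Working it through.** **The plan's own figure.** Inputs from Sample size: difference 10, SD 26.27, two-sided α=0.01, power 80%, drop-out 10%.

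- Normal approximation: n = 2 × (2.576 + 0.842)² × 26.27² / 10² ≈ 161.2, so 162. The t-test solution is 162.9, so 163, as stated.
- 163 / 0.90 = 181.1, so 182 per arm; 3 × 182 = 546, as stated.

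The 0.01 level is thus built into a VHI calculation. Three tests at 0.01 sum to 0.03; an equal Bonferroni share of 0.05 would be 0.05/3 = 0.0167.

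**Which splits fail 0.01?** The article gives no adverse-event rate, and the pilot saw no vocal strain or abuse, so the counts below are illustrations with 182 per arm. For 6 versus 0:

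- pooled proportion = 6/364 = 0.01648
- standard error = √(0.01648 × 0.98352 × 2/182) = 0.01335
- z = (6/182)/0.01335 = 2.47, two-sided p = 0.0135

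| Events | Chi-squared p (uncorrected) | Fisher p |
|---|---|---|
| 4 v 0 | 0.044 | 0.123 |
| 5 v 0 | 0.024 | 0.061 |
| 6 v 0 | 0.0135 | 0.030 |
| 7 v 0 | 0.0075 | 0.015 |
| 8 v 0 | 0.0042 | 0.007 |
| 9 v 1 | 0.0103 | 0.020 |
| 11 v 2 | 0.0110 | 0.020 |

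Against zero, significance at 0.01 needs 7 events by chi-squared and 8 by Fisher. At 0.05 it needs 4 and 6. With 163 per arm the p values barely change (6 v 0: 0.0134; 9 v 1: 0.0102).

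**Interval beside verdict, 9 versus 1.** RR = 9.0. SE of log RR = √(1/9 − 1/182 + 1/1 − 1/182) = 1.049. The 95% CI is exp(2.197 ± 1.96 × 1.049) = 1.15 to 70.3. The interval excludes 1 while the test fails 0.01. For 11 versus 2, RR is 5.5 with 95% CI 1.24 to 24.5, and the test again fails 0.01.

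**Power, by binomial enumeration at assumed true rates.** For 3% versus 0% the control count is always zero, so power is a binomial tail with X ~ Bin(182, 0.03):

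- chi-squared: P(X ≥ 7) = 0.306 at 0.01; P(X ≥ 4) = 0.798 at 0.05
- Fisher: P(X ≥ 8) = 0.183 at 0.01; P(X ≥ 6) = 0.465 at 0.05

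| Assumed rates | Chi-squared, 0.01 / 0.05 | Fisher, 0.01 / 0.05 |
|---|---|---|
| 2% v 0% | 7.5% / 49.5% | 3% / 16% |
| 3% v 0% | 31% / 80% | 18% / 47% |
| 5% v 1% | 32.5% / 63.5% | 24% / 51% |
| 8% v 1% | 79% / 94% | 72% / 90% |

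**The case against.** Three stronger readings are tempting, and the article does not support them.

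- *That it says outright that adverse events are judged at 0.01.* It does not. The all-tests wording governs the sentence on summary statistics and intervals; the threshold is in the next sentence. Coverage of harms is an inference. It is nevertheless the natural one, because adverse events are a listed secondary outcome, are tested under the secondary analyses, and have no other level.
- *That 0.01 is a correction meant for efficacy claims.* The stated reason is the number of treatment comparisons, and harms are compared across the same three pairs. Leaving harms out of multiplicity control is a sound convention, but the plan does not contradict itself by omitting to do so.
- *That a real excess would be hidden.* Counts and percentages are reported whatever the p value, and the intervals are already unadjusted at 95%. No interim analysis is planned, and no stopping rule or safety conclusion is tied to the test.

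Two further objections concern size and scope. The uncorrected chi-squared test is unreliable with these counts (6 versus 0 means an expected 3 per arm), so its 80% power at 0.05 flatters the alternative. Fisher's test is weak even at 0.05, and sparse events are the larger limit. This stands, although the loss in moving to 0.01 appears under both tests. Lastly, the level for safety p values might be left to the SAP. That would answer a silence, but here a rule is stated without exception.

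**Conclusion.** The point holds as a minor one. On the natural reading, a level sized on VHI and tightened for three treatment comparisons also decides the verdict on adverse events, and this reduces sensitivity to the one harm the protocol names. At assumed rates of 3% versus 0%, the loss is about 49 percentage points by uncorrected chi-squared (80% to 31%) and about 28 by Fisher (47% to 18%). Splits such as 6 versus 0 and 9 versus 1 would be labelled non-significant.

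These sizes rest on assumed rates, 182 analysed per arm, and the threshold being applied to harms as written. The planned descriptive reporting limits the consequence to how the result is labelled and read. The VHI analysis is unaffected.

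**What to change.** In Statistical analysis, restrict the p<0.01 criterion to the efficacy outcomes. In Secondary outcome analyses, state that adverse events are interpreted from counts, risk differences and relative risks with 95% confidence intervals, using exact methods where counts are small or one arm has no events. Any p value should be given without a significance verdict, and a large one should not be read as absence of harm.

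The cost is a sentence or two in the protocol or SAP. Sample size, data collection and efficacy analyses stay as they are. The small downside is more chance flags among harms.
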